### Data analysis

A composite score will be calculated based on measures from birth to 24 months post-birth, similar to our composite measure in our previous RCT in Cape Town [33, 34]. It will be a sum of assessments of the attainment (1) or not (0) of well-being from 10 indicators of MCH. Outcomes will be assessed as present (1) or absent (0). Base rates influence the number of significant outcomes needed on individual domains to yield a significant result. To examine overall differences between MCH outcomes in the SC in contrast to the AC, a single index summing the 10 indicators will be calculated as the sum of 1 s, reflecting a score above the median (e.g., on months of breastfeeding) or present (getting all immunizations, attending > 3 antenatal visits), or 0 s, reflecting a score below the median or not present (e.g., no child grant, no maternal HIV testing in pregnancy).

The primary analyses will examine cumulative change across multiple indicators of maternal and infant health. For outcomes only assessed at 24 months, differences between AC and SC conditions will be examined using random effects regression models to control for neighborhood clustering. Differences between outcomes assessed at baseline, 6, 15, and 24 months will be explored using multi-level models adjusting for repeated measures and neighborhood effects. Data analysis will be conducted using SAS software version 9.2 [50]. Linear regression will be used for continuous variables, and logistic regression and Poisson/negative binomial regression will be implemented for binary and count outcomes, respectively. Logistic regression will be used for longitudinal binary outcomes.

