**Methods/Design:**

In the deeply rural, Eastern Cape of South Africa, CHW will be hired by the government and will be initially trained by the Philani Programme to conduct home visits with all pregnant mothers and their children until the children are 2 years old. Eight clinics will be randomized to receive either (1) the Accountable Care Condition in which additional monitoring and accountability systems that Philani routinely uses are implemented (4 clinics, 16 CHW, 450 households); or (2) a Standard Care Condition of initial Philani training, but with supervision and monitoring being delivered by local government structures and systems (4 clinics, 21 CHW, 450 households). In the Accountable Care Condition areas, the CHW’s mobile phone reports, which are time-location stamped, will be monitored and data-informed supervision will be provided, as well as monitoring growth, medical adherence, mental health, and alcohol use outcomes. Interviewers will independently assess outcomes at pregnancy at 3, 6, 15, and 24 months post-birth. The primary outcome will be a composite score of documenting maternal HIV/TB testing, linkage to care, treatment adherence and retention, as well as child physical growth, cognitive functioning, and child behavior and developmental milestones.

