### Assessments

Independent assessments will be conducted by Stellenbosch University during pregnancy, within 3 months of birth, and at 6, 15, and 24 months post-birth. The PIM is a generalist model. Therefore, there is a cluster of both maternal outcomes and child outcomes. Table 1 summarizes these measures, with the source of the data to determine accomplishment (1) or not (0) of each outcome. Assessors will conduct interviews and gather additional information from health case files, as well as the child’s government-issued, Road-to-Health card. All data will be entered on mobile phones with preprogrammed responses and sent encrypted to a data center. Data for identification will be stored separately from the assessment data. Assessment data will be coded with personal identification numbers and will not include any personally identifiable data. De-identified assessment data will be available through a password-protected, cloud-based database and accessed by UCLA and Stellenbosch University for quality control and, later, analysis. The risk of gathering information with properly trained and supervised staff poses minimal risk to the proposed participants. There are no physical risks associated with participation.

**Table 1 Tab1:** Outcomes assessed independently during pregnancy, within 3 months of birth, and at 6, 15, and 24 months post-birth scored by the attainment (1) or not (0) of well-being from 10 indicators of maternal and child health

Outcome	Measure
For Mother	
Adherence to medical regimes	Clinic records and self-reports; for mothers living with HIV, there are six prevention of mother-to-child transmission tasks, re-engagement in HIV care post-birth, receipt and adherence to antiretroviral medications over the last week
Breastfed for 6 months (mixed ok)	Self-report and home observations
Alcohol use (AUDIT-C > 2)	Breathalyzer and self-reports
Mental health (EPDS > 13)	Self-reports
For Children	
Growth in height (< −2 SD)	Measurements; tape measures and measuring boards calibrated biweekly
Growth in weight (< −2 SD)	Measurements; scales calibrated biweekly
Adherence to medical regimes	Clinic records, self-report, including for diarrhea, immunizations, respiratory illnesses
Number of hospitalizations and clinic visits	Clinic records, self-reports
WHO Developmental scale in normal range	Assessment of child and maternal reports
Bayley scale in normal range (24 months only)	Assessment of the child

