Child Behavior Checklist in normal range on all scales	Maternal reports

Alcohol Use Disorders Identification Test-Clinical Utility (AUDIT-C)

Edinburgh Perinatal Depression Inventory (EPDS)

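### The primary composite is stated inconsistently: 10 indicators are announced but 11 are listed, and the items, scoring rule, time window and type of outcome differ between sections

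*Protocol article*

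**What the plan says.** The Data analysis section defines the primary composite as a sum of 0/1 indicators and states their number twice, once in the words "a single index summing the 10 indicators will be calculated". The Table 1 caption (Assessments) gives the same number: outcomes are "scored by the attainment (1) or not (0) of well-being from 10 indicators of maternal and child health".

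Table 1 then lists its items, the last being "Child Behavior Checklist in normal range on all scales". Several carry fixed criteria, for example "Breastfed for 6 months (mixed ok)" and "Alcohol use (AUDIT-C > 2)". The maternal adherence row draws on clinic records and self-reports and adds that "for mothers living with HIV, there are six prevention of mother-to-child transmission tasks", together with HIV care after birth and antiretroviral adherence.

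Three other places describe the same outcome:

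- **Abstract, Methods/Design.** The primary outcome is a "composite score of documenting maternal HIV/TB testing, linkage to care, treatment adherence and retention", together with child growth, cognition, behavior and milestones.
- **Data analysis.** The composite uses measures between birth and 24 months. An indicator scores 1 if above the median (months of breastfeeding is the example) or if present (all immunizations, more than three antenatal visits). It scores 0 if below the median or not present ("e.g., no child grant, no maternal HIV testing in pregnancy").
- **Power calculations.** The primary outcome is a measure that adds up how many individual outcomes are significant.

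**The concern.** A primary endpoint has to be one variable that any analyst would build in the same way from the text. Here the number of items, their identity, the cut-offs and the time window are not the same from section to section, and the power section describes a different kind of quantity.

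The candidate items also differ in kind. Some are services that reminders from a supervised health worker could readily affect, such as a grant, a test or a visit. Others are child growth and development. Which items enter the sum could therefore change both the size of the effect and its meaning. If the list were settled only after outcome data had been seen, the nominal 5% error rate would no longer be secure.

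**Working it through.** **1. Count of the indicators.** The stated figure is 10 (Table 1 caption; Data analysis, twice). The rows of Table 1 are:

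- Mother: medical adherence, breastfeeding, alcohol, mental health = 4.
- Child: height, weight, medical adherence, hospitalizations and clinic visits, WHO developmental scale, Bayley, Child Behavior Checklist = 7.
- Total: 4 + 7 = 11. The stated 10 is not reproduced.

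**2. Readings that might give 10.**

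- Drop the Bayley because it is marked as a 24-month measure: 11 − 1 = 10. But the Development section also places the Child Behavior Checklist at 24 months. On that logic 11 − 2 = 9 rows apply before 24 months and 11 at 24 months, never 10.
- Merge height and weight into one growth item: 11 − 1 = 10. But the table gives them separate rows with separate criteria.

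No sentence in the article selects either reading.

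**3. Data analysis examples set against Table 1.**

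| Example | Place in Table 1 |
|---|---|
| Months of breastfeeding | A row, but with a fixed 6-month criterion instead of the median |
| All immunizations | Inside the child adherence row |
| More than three antenatal visits | Not named; at most read into maternal adherence |
| HIV testing in pregnancy | Not named; at most read into maternal adherence, via the General health section under Maternal assessments |
| Child grant | None |

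Two of the five have a home, two are arguable and one is clearly outside. The two arguable items occur in pregnancy, before the window that the same section sets for the composite.

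**4. Abstract set against Table 1.** Linkage, adherence and retention correspond to maternal adherence (1 row), growth to height and weight (2), cognition to the Bayley (1), behavior to the Child Behavior Checklist (1) and milestones to the WHO scale (1). That covers 6 of 11 rows. Breastfeeding, alcohol, mental health, child adherence, and hospitalizations and clinic visits (5 rows) are not mentioned. HIV and TB testing are named although Table 1 lists neither. TB testing appears nowhere else in the article.

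**5. Type of quantity.** The Data analysis section describes a sum of 0s and 1s for each participant. The power section describes a number of significant tests, which is one figure for the whole trial. These are different statistics with different null distributions.

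**6. Illustration of what selection could do.** Simulation under no effect, with 450 × 0.8 = 360 participants per arm, 3,000 trials per setting, item rates of 0.5 to 0.9 and latent item correlation of 0.05 to 0.2. The rates and correlations are assumed, and clustering is ignored.

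- One fixed 11-item sum: about 5%.
- Best of three natural readings (all 11 rows; without the Bayley; height and weight merged): about 5 to 8%.
- Best of all 11 sums that leave out one row: about 9 to 13%.

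**The case against.** The strongest defence is that the lists overlap more than they conflict. The abstract mostly condenses Table 1, and omissions from a one-sentence summary are weak evidence of a rival definition. The Data analysis items illustrate 0/1 scoring and are not offered as a full list; two of them fit Table 1, and two more could be components of maternal adherence. A reader might infer three wholly competing definitions of the endpoint, but the documents do not support that.

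A reader might also infer that the false-positive rate is in fact 10% or more. That does not follow. It would require an analyst to try many versions and keep the best, which the plan nowhere proposes. The rates also rest on assumed inputs, and the higher ones include arbitrary versions, such as leaving out depression alone.

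Nor can one say that TB testing cannot be scored. The supportable statement is that the article describes no measure for it.

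Finally, this is a condensed article, and an analysis plan that is not shown may fix the list. That would excuse missing detail. It does not excuse statements that disagree: 10 against 11 rows, the child grant, TB testing, the median against a fixed criterion, the window from birth against antenatal items, and the wording of the power section. Any later document would have to overrule some of these.

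**Conclusion.** The concern holds as an internal inconsistency about the primary endpoint. The certain parts need no assumptions: 11 rows against a stated 10; one Data analysis item (child grant) with no place in Table 1; two antenatal items not named there and outside the stated window; one abstract item (TB testing) with no described measure; two scoring rules for breastfeeding; and a power section that describes another kind of outcome.

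The consequence is that two analysts following the text could compute different primary endpoints. The direction and size of the difference cannot be derived from the article. The simulated error rates are illustrative only and should not be quoted as a property of the trial. Because the primary endpoint is affected, the text must be corrected.

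**What to change.** Before recruitment, which the Trial status section says had not begun at submission:

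1. Adopt one numbered list of items, with one scoring rule, data source and time point for each. Either change 10 to 11 in the Table 1 caption and the Data analysis section, or name the row that is removed or merged.
2. State whether the child grant, antenatal visits and maternal HIV testing belong to the composite or are secondary outcomes. If the antenatal items belong, change the time window to include pregnancy.
3. Choose the median or the fixed criterion for breastfeeding, and say which items, if any, use a median split.
4. Remove TB testing from the primary outcome in the abstract, unless a measure and data source are already planned. If they are, describe them.
5. Rewrite the abstract sentence and the power section so that both describe the same per-participant score. If a count of significant outcomes is really intended, say so and change the Data analysis section to match.

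Adopting Table 1 as the sole list would not be enough, because the median rule, the time window and the power section would still disagree with it. The cost is wording only, provided no item that is not already measured, such as TB testing, is added.

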### Setting

The OR Tambo District is a rural, hilly area in the Eastern Cape of South Africa accessible on a 150 km paved road east from Umtata and north of East London, with very high unemployment. The area is ancient tribal land, with the tribe allowing only minimal industrialization. Zithulele Hospital serves 130,000 families with nine local clinics. To reach clinics, a patient must cover large distances of hilly terrain either by walking or using the expensive and infrequent mini bus taxis. Aerial maps provided information on the density of each potential study area.

With the support of the District Health Officer, the team has documented the catchment areas of each CHW assigned to eight clinics in the catchment area of Zithulele Hospital. Data on access to electricity (8% in the region), water tanks (16%), flush toilets (few), distance from the road and the local clinics, and hilliness was used to identify areas of about 200 households each. The areas were matched by UCLA and all CHWs at each clinic (3–5 per clinic) were randomized to either (1) the Accountable Care (AC) condition, in which the PIM supervision and training models will be implemented (4 clinics, 16 CHW, 450 households); or (2) Standard Care (SC) by existing government supervisors and CHWs implementing home visits (4 clinics, 21 CHW, 450 households). Risk of contamination is very low given it is a deeply rural region with vast distances between villages and even homes. Figure 2 outlines the design of the randomized controlled trial (RCT), with the planned follow-up assessments by an independent team of assessors.

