**Fig. 2 Fig2:**
[figure not shown]
Description of the RCT for area randomization by UCLA to one of two conditions

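### Clinics are the randomised unit, but the models adjust only for an undefined neighbourhood level; if that means the health-worker areas, clinic variance is missing from the standard error

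*Protocol article*

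**What the plan says.** On the unit of randomisation, the abstract (Methods/Design) states "Eight clinics will be randomized to receive either" of the two conditions. The Setting section says "all CHWs at each clinic (3–5 per clinic) were randomized to either" arm, and describes the AC arm as "4 clinics, 16 CHW, 450 households"; the SC arm has 4 clinics, 21 CHWs and 450 households. The Fig. 2 caption is worded differently: "Description of the RCT for area randomization by UCLA to one of two conditions".

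On smaller units, the Setting section reports that the catchment area of each CHW was mapped, that local data "was used to identify areas of about 200 households each", and that these areas were matched.

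On the models, the Data analysis section says that for outcomes measured only at 24 months "differences between AC and SC conditions will be examined using random effects regression models to control for neighborhood clustering". For outcomes measured repeatedly it plans "multi-level models adjusting for repeated measures and neighborhood effects". Neither sentence names a clinic term, and neighbourhood is not defined.

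The Power calculations section assumes an ICC of 0.01 for areas and 80% retention, and states power of 0.80 at an effect size of 0.21. It gives neither a number of clusters nor a clinic-level ICC.

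**The concern.** The random effect should include the unit that was allocated. Whatever the women of one clinic share, beyond what their CHW area explains, is common to all areas of that clinic, and those areas are all in one arm. A model with area intercepts only treats that shared part as independent from area to area. The standard error of the AC-versus-SC difference is then too small, and the test refers to roughly 35 degrees of freedom (37 areas less 2) where the design supports about 6 (8 clinics less 2). The risk is a false claim that supervision and accountability work.

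This is more than detail left to a fuller analysis plan. The article itself names the clustering level, and that level does not match the unit that it says was randomised.

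**Working it through.** **Inputs.** 450 households per arm and 80% retention give 360 per arm, 720 in all. There are 8 clinics, so 720/8 = 90 analysed per clinic. There are 16 + 21 = 37 CHWs; one area each is inferred, so 720/37 = 19.46 per area. ICC 0.01, alpha 0.05 (two-sided assumed), power 0.80.

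**Step 1: the plan's own figure.** Detectable effect = (1.960 + 0.842) × √(2/n × DEFF), with DEFF = 1 + (m − 1) × ICC and n per arm.

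- 37 areas: DEFF = 1 + 18.46 × 0.01 = 1.185; effect = 2.802 × √(2/360 × 1.185) = 0.227; power at 0.21 is 0.735.
- 8 clinics: DEFF = 1 + 89 × 0.01 = 1.89; effect = 2.802 × √(2/360 × 1.89) = 0.287; power at 0.21 is 0.536.

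The stated 0.21 follows from neither. It appears if the ICC is ignored (0.209), or if 37 areas are used without retention loss (0.207).

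**Step 2: which level the power section had in mind.** The article states subgroup effects of 0.31 (half the sample) and 0.38 (a third).

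| Clusters | Half | Third |
|---|---|---|
| 37 areas | 0.308 | 0.371 |
| 8 clinics | 0.354 | 0.411 |
| Stated | 0.31 | 0.38 |

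The match to 37 areas is not exact for the third, but both figures lie much nearer to area-level than to clinic-level clustering.

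**Step 3: type I error of an area-only model.** If areas are nested in clinics, the correlation within an area is the clinic share plus the area share. A stated area ICC of 0.01 therefore bounds the clinic share between 0 and 0.01. The true design effect is 1 + 89 × (clinic share) + 18.46 × (area share). The area-only model assumes 1.185 whatever the split. The test statistic is inflated by the square root of the ratio.

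- All at clinic level: √(1.89/1.185) = 1.263; 1.96/1.263 = 1.552; two-sided error 12.1%.
- Even split: true DEFF = 1 + 0.445 + 0.092 = 1.537; √(1.537/1.185) = 1.139; error 8.5%.
- All at area level: ratio 1; error 5%.

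Simulation of an area-random-intercept model fitted by REML (20,000 runs, one continuous outcome, 720 women, clinics with 4, 4, 4, 4, 5, 5, 5 and 6 areas) agrees. The range runs from a t reference with 35 df to a normal reference.

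| Clinic share | Area share | Area-only model | Clinic means, t on 6 df |
|---|---|---|---|
| 0 | 0.01 | 4.4–5.2% | 5.0% |
| 0.0025 | 0.0075 | 5.8–6.6% | 4.8% |
| 0.005 | 0.005 | 7.9–9.0% | 5.1% |
| 0.0075 | 0.0025 | 9.3–10.4% | 5.1% |
| 0.01 | 0 | 11.5–12.6% | 5.2% |

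**Step 4: power with the clinic as cluster.** With a clinic ICC of 0.01, power at 0.21 is 0.54 against a normal reference and 0.41 against t on 6 df. The detectable effect is 0.287 or 0.345.

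**The case against.** The strongest reply is that neighbourhood is undefined. The Setting section never calls its 200-household areas neighbourhoods, and the Fig. 2 caption uses area for the randomised unit. If neighbourhood means that unit, the model is right and only the wording is loose. It is fair that the CHW-area reading is an inference and that 37 is nowhere given as a count of areas. But reading neighbourhood as clinic does not rescue the plan, because the stated power then fails (Step 4). Reading areas as the allocated unit contradicts the abstract and the Setting section.

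Several stronger statements are tempting and are not supported:

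- *The type I error at least doubles.* Doubling is near the top of the range that the stated ICC allows. With a quarter of the correlation at clinic level the error is about 6 to 7%, and with none there is no inflation.
- *The error reaches 17% or 26%.* Such figures need clinic ICCs of 0.02 or 0.05, which exceed the stated area ICC and are outside assumptions.
- *These percentages are the error rate of the primary test.* They are for one continuous outcome. The Power calculations section describes the primary measure as a count of significant individual outcomes.
- *Clinic variation lies wholly between the arms.* With four clinics per arm it also shows within arms, which is what makes a 6-df test possible.
- *Every moderator analysis is equally affected.* Baseline moderators such as HIV status vary within clinics, so a shared clinic intercept largely cancels from those interaction contrasts.

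The article also does not specify a normal reference distribution, so it cannot be faulted for choosing one.

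**Conclusion.** The concern holds in conditional form. The allocated unit is the clinic, and the written models name only a level that is most likely smaller. On that reading the AC-versus-SC test is anti-conservative whenever any correlation sits at clinic level: about 5% to 12% actual error at a nominal 5%, given the stated ICC of 0.01. It would be higher only if the clinic ICC exceeds 0.01, which the document neither states nor rules out.

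A clinic share of exactly zero would be a bold assumption. Table 1 draws maternal adherence, child adherence and the hospitalisation and visit counts partly from clinic records, and SC mothers are referred to local clinics for testing.

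The result rests on one area per CHW, two-sided testing, near-equal clinic sizes and a continuous outcome. On any reading, the randomisation, modelling and power statements cannot all stand together.

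**What to change.** 1. Define neighbourhood, and state one unit of randomisation consistently in the abstract, the Setting section and the Fig. 2 caption.
2. In the AC-versus-SC models, include a random intercept for clinic with CHW area nested within it.
3. Test the arm effect with small-sample, between-cluster degrees of freedom: about 6, or fewer if the matching described under Setting is modelled. A comparison of clinic means is an acceptable alternative; it held 4.8 to 5.2% in the simulations above.
4. Restate power for eight clusters, with an explicit clinic-level ICC and a range around it. At a clinic ICC of 0.01 and 90 analysed per clinic, the detectable effect is about 0.29 to 0.35 rather than 0.21.

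Adjustment for baseline covariates is optional and not needed for this point.

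The change to the models is small and needs no new data; recruitment had not begun when the article was submitted. The real cost is wider confidence intervals and a visibly less favourable power statement.
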